#### 13.6. PATIENT'S INFORMATION AND INFORMED CONSENT

The investigators must ensure that the patients have received all relevant information, orally or in writing, relating to the type, objective and possible risks and benefits of the study. Patients must also be informed that they are free to withdraw from the study at any time.

The information will be given in reasonable time before study start.

The investigators must obtain written informed consent from the patients prior to their enrolment in the study. The information given to the patient must be attached to the written informed consent.

If modifications are needed according to local regulations, or if new information becomes available (e.g. from Sponsor) that can significantly affect a subject's future health and medical care, a new version of the "Patient information and informed consent" must be prepared in cooperation with investigator(s) and approved by

Gambro. The new version of the "Patient information and informed consent" shall be given to each enrolled patient for information and agreement.

#### **13.6.1. General process for obtaining informed consent**

The general process for obtaining informed consent will be followed by Sponsor and Investigator and shall:

- a) Ensure that the principal investigator or his/her authorized designee conducts the informed consent process,
- b) Include all aspects of the clinical investigation that are relevant to the subject's decision to participate throughout the clinical investigation,
- c) Avoid any coercion or undue improper influence on, or inducement of, the subject to participate,
- d) Not waive or appear to waive the subject's legal rights,
- e) Use native non-technical language that is understandable to the subject,
- f) Provide ample time for the subject to read and understand the informed consent form and to consider participation in the clinical investigation,
- g) Include personally dated signatures of the subject and the principal investigator or an authorized designee responsible for conducting the informed consent process,
- h) Provide the subject with a copy of the signed and dated informed consent form and any other written information,
- i) Show how informed consent will be obtained and recorded in special circumstances where the subject is unable to provide it him- or herself, and
- j) Ensure important new information is provided to new and existing subjects throughout the clinical investigation.

### **14. ARCHIVING OF STUDY DOCUMENTATION**

The investigators must keep essential study documents (including all original raw data together with the patients' identification list and signed informed consents) minimum 5 years after product commercialization is stopped and should be retained for a longer period however if required by the applicable regulatory requirements or by an agreement with the sponsor.

Patient medical files have to be kept as much as possible at each investigation site.

Investigators will be informed by Sponsor when documents related to the study could be deleted. Prior to destroying study-related documentation, the investigator shall make sure with the Sponsor, which it does not need to be kept any longer.

### **15. INVESTIGATIONAL PROCEDURES**

#### **15.1. TRAINING**

The Gambro Study Monitor(s) will ensure that hospital staff involved in the study (namely Principal Investigator team, Pharmacy, Laboratory) receives appropriate training for the purpose of the study.

Both Gambro and the investigators must make sure that sub-investigators and any other staff participating actively in the study have been appropriately trained and received the relevant information relating to the performance of this study.

If needed, a second training can be organized on study site request for clarification purposes.

All trainings shall be recorded in a Training Log and file in the Study Master File and respective Master files (e.g. Investigator Site File).

## 15.2. MONITORING

During the course of the study the Gambro monitor(s) will have regular contacts with the study sites and will make regular visits to get an overseeing of the clinical study. Before the patient enrolment starts and during the course of the study, the Gambro monitor(s) will ensure that clinical facilities are acceptable, that the accountability of the investigational and comparator product is performed, that the clinical study is conducted, recorded, and reported in accordance with the protocol, written procedures (see CTF BG 003 Study Monitoring Process), the current regulation linked to the investigational or comparator product type (see § Ethics and Regulatory Issues), and the applicable local regulatory requirements. The Gambro monitor(s) will also ensure that source data are available and that the study results are properly recorded in CRFs.

By signing the protocol, the investigators agree to allocate their time and the time of their staff to discuss findings and any relevant issues during the monitoring visits.

The study monitor must fill in a monitoring report at each study visit according to the monitoring procedure. The monitoring report will include namely information on the following:

- Patient's informed consent obtained prior to the start of the study,
- Patient's status (enrolled, included, withdrawn and completed),
- Verification of source data according to the monitoring check-list,
- Compliance with inclusion and exclusion criteria according to the monitoring check-list,
- Compliance with sampling procedure,
- Potential deviation from protocol (namely if the deviation affects subject's rights, safety and wellbeing, or the scientific integrity of the clinical investigation),
- Safety issues (i.e. potential observed AE, SAE, Device Deficiencies and Other Observations).

### 15.2.1. Deviations from clinical investigation plan

The investigator is not allowed to deviate from the protocol. Under emergency circumstances, deviations from the protocol to protect the rights, safety and well-being of human subjects may proceed without prior approval of the sponsor and the EC. Such deviations shall be documented and reported to the sponsor as soon as possible.

- The Study Monitors specify in the Monitoring Visit all deviation from protocol (namely if the deviation affects subject's rights, safety and wellbeing, or the scientific integrity of the clinical investigation),
- The Study Manager checks the pertinence of the deviation,
- 
- If a deviation is effective, the Investigator shall be informed (formal letter) to prevent potential future deviation, and the deviation is listed in a table (see CTF BG 004 "Data Management"),
- 
- The Deviation table shall be taken into account during the final data review (Adherence Review Meeting).

## 15.3. DIRECT ACCESS TO SOURCE DOCUMENTS

The investigator must give the Study Monitor direct access to relevant hospital or clinical records to confirm their consistency with the CRF entries. No information in these records about the identity of the subjects will leave the study site. Gambro monitoring standards require full verification for the presence of informed consent, adherence to the inclusion/exclusion criteria, documentation of AEs/SAEs and Device Deficiencies and the recording of primary efficacy and safety variables. Additional checks of the consistency of the source data with the CRFs are performed according to the study-specific monitoring plan.

#### 15.4. SOURCE DATA VERIFICATION

By signing the protocol, the investigators agree to allocate their time and the time of their staff to discuss findings and any relevant issues linked to source data.

A study-specific monitoring plan specifies which and whether other parameters need to be verified by 100%

The data to be compulsorily checked are the following:

- Inclusion and exclusion criteria,
- Adverse Events, Serious Adverse Events and Device Deficiencies (for MD),
- Concomitant medication (when possible effect on evaluated parameters),
- Main criteria laboratory data.

Note: Study Manager can decide to adapt the % of verification of parameters during the study.

#### 15.5. AUDITS AND INSPECTIONS

In addition to the routine monitoring procedures and in accordance with Good Clinical Practice (GCP) principles, GCP audits might well be performed by the Quality Assurance members of Gambro. These audits of clinical research activities are in accordance with applicable regulatory requirements, Gambro internal policies and procedures, to evaluate compliance with the principles of GCP. A Regulatory Authority may also wish to conduct an inspection (during the study or even after its completion). If a Regulatory Authority requests an inspection, the investigator must immediately inform the Study Monitor of Gambro that this request has been made.

### 16. STUDY ORGANIZATION

#### 16.1. INVESTIGATORS

The investigators taking part in the clinical study are nephrologists with wide experience in the field of renal replacement therapies including HD treatments. They already have experience in conducting clinical studies according GCP.

Sponsor shall receive disclosures of conflict of interest from coordinating investigators, principal investigators and sub-investigators, where required by national regulations.

##### 16.1.1. Coordinating and Principal Investigators

See page 1-3 or “Contact List”

#### 16.2. STUDY ADMINISTRATION

Gambro has established a study team comprising a Study Manager and Study Monitor (see Contact List). This study team missions are to ensure the compliance with protocol by following GCP as well as planning follow-up.

##### 16.2.1. Steering Committee

The Steering Committee is the main policy and decision making committee of the study and has final responsibility for the scientific conduct. The Steering Committee is free to choose and invite any expert they regard as necessary. Contact details of the Steering Committee are presented in the “Contact List”.

##### 16.2.2. Data Safety Monitoring Board (DSMB)

Not applicable

### 16.3. OTHER STUDY CONTACTS

#### 16.3.1. CRO

Contact details of the CRO KKS Halle are presented in the “Contact List”

## 17. STATISTICAL METHODS

### 17.1. POPULATION SIZE ESTIMATION

#### 17.1.1. Sample size calculation

The sample size estimation is based on results of the Perci 1 Study. In this study we found an effect size (intraindividual difference of means divided by intraindividual standard deviation) of about 0.5 for the TNF alpha expression. Assuming a power of 80%, a level of significance of 0.05 (two-sided) we need 34 evaluable patients. Taking into account a 30% drop out rate we have to allocate 50 patients to obtain 35 evaluable patients. This number is based on an observed drop-out rate of 20% in the Perci 1 study with shorter study duration. Note that the primary analysis will be done baseline adjusted and we expect an increase of power due to this adjustment. Further, we expect that the decrease of variance due to stratification and baseline adjustment will more than outweigh the loss of degrees of freedom due to adjustment and stratification.

#### 17.2. CODING

All AEs will be categorized by the Medical Dictionary for Regulatory Activities (MedDRA).

#### 17.3. STATISTICAL ANALYSIS

A complete description of the statistical analysis will be presented in the Statistical Analysis Plan which should be final, approved and signed before database clean file.

#### 17.4. STATISTICAL ANALYSIS

A complete description of the statistical analysis will be presented in the Statistical Analysis Plan which should be final, approved and signed before database clean file.

Primary analysis:

The primary analysis compares the expression values of TNF alpha intraindividually between both membranes. The null hypothesis and alternative are

H0: There is no difference between both membranes regarding the expression of TNF alpha

H1: There is a difference between both membranes regarding the expression of TNF alpha

Even so the alternative is formulated undirected and the significance testing will be carried out two-sided we expect superiority of HCO vs the control membrane, i.e. lower expression rates for the HCO membrane. The analysis will be done by testing the main effect of treatment in a GEE (Generalized Estimating Equations) model with baseline adjustment, including effects for time and centre as additional covariates. The level of significance is 0.05 (two-sided).

Study populations

In a blind data review (see below) each patient will be assigned to a study population

PP includes all patients treated according to the study protocol including those with minor deviations to be defined before the blind data review

(Modified) ITT includes additionally to PP all patients with measurements from at least one study phase and no clinical events which make measurement of primary endpoint impossible

Full Set includes all randomized patients

Safety includes all patients which received at least one intervention

#### Primary analysis population:

The primary analysis population will be the modified ITT population. Patients with clinical events making the analysis of the primary endpoint impossible will be excluded after a blind data review. The remaining drop outs will be included in the analysis if results are available for at least one treatment phase.

#### Secondary analyses

The secondary analyses include the analysis of the primary endpoint in the per protocol population. Secondary outcome variables will be analysed in the same way as the primary endpoint, using generalized linear models and the method of GEE as described above.

#### Descriptive analyses

The description includes means, medians, standard deviations, quartiles and ranges according to scaling and distribution of the variables. Graphical descriptions include line graphs displaying the individual measurement over time for each patient and box plots.

#### Exploratory analyses

1. In exploratory analyses we will investigate which measurements at baseline might be prognostic for the performance of the several membranes. This analysis will be, however, of limited power due to the moderate sample size.
2. The analysis of Phase 3 of the trial (prolongation of treatment after the termination of the second period of the cross over design) will be exploratory. Analysis will be done using generalized estimating equations including a three level factor for time and the two level factor for treatment. The primary hypothesis within this analysis is the treatment effect. Baseline will be adjusted for analogously to the primary analysis. Time vs treatment interaction will be investigated.

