## 1.3. JUSTIFICATION OF TREATMENT PERIODS AND EVALUATION SCHEDULE

Since the MCO membrane has a nearly similar removal capacity for molecules up to 45 kDa as the HCO membrane we justified the treatment period based on the experiences of clinical studies with HCO1100. In the PERCI study (unpublished data) we detected mRNA levels of TNF- $\alpha$  and IL-6 to be significantly reduced after 3 weeks treatment period. Among the soluble inflammation mediators, some were reduced by 3 weeks of treatment, some were not. However the reduction of serum levels of several soluble inflammation mediators was

more pronounced after three weeks of treatment compared to two weeks. We therefore have chosen a 4 weeks treatment period for the primary endpoint TNF- $\alpha$  mRNA for this study.

Since the reduction of pre-dialytic values of soluble inflammatory molecules (secondary endpoints) is expected to take longer, a 12 weeks prolonged treatment period has been chosen to follow pre dialytic values of inflammatory mediators.

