### **3.2. SECONDARY ENDPOINTS**

- Safety events (SAE, AE, DD, other observations)

- Routine laboratory diagnostic parameter

- IL-6 mRNA expression level in PBMC after 4 weeks (T1/T3 versus T4/T6) and 3 month treatment (T7)

- TNF- $\alpha$  mRNA expression level in PBMC after 3 month treatment (T7)

- Kinetics of selected uremic toxins during one dialysis session (with a subset of 10 patients only at the study site Halle)
- Change of plasma proteins (explorative markers) after 4 weeks (T1/T3 versus T4/T6) and 3 month treatment (T7).
- Experimental ex vivo analysis of patient plasma and dialysis fluid (proteomics, effects on cellular assays, AGEs)
- Change of  $\mu$ RNA (explorative markers) after 4 weeks (T1/T3 versus T4/T6) and 3 month treatment (T7).

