#### 4.2. STUDY PERIODS

The study will be divided in five steps as describes in the figure below:

- Run in phase
- Phase 1
- Wash out phase
- Phase 2
- Phase 3

Note that Phase 3 is not part of the cross over design.

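### The Phase 3 hypothesis is a treatment effect pooled over three time points, not the T7 effect that defines the 3-month endpoints, and T7 is classed both as secondary and as exploratory

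*Protocol*

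**What the plan says.** Protocol 17.4, under exploratory analyses, gives Phase 3 its own model: a GEE "including a three level factor for time and the two level factor for treatment. The primary hypothesis within this analysis is the treatment effect". It adds baseline adjustment on the pattern of the primary analysis and says that the interaction of time with treatment will be looked at. It does not say which three time points form the factor.

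The 3-month endpoints are defined at one time point. Section 3.2 lists TNF-α "mRNA expression level in PBMC after 3 month treatment (T7") as a secondary endpoint, and IL-6 mRNA, plasma proteins and µRNA at T7 likewise. Section 1.3 gives the reason for the longer phase: soluble mediators are expected to fall more slowly, so "a 12 weeks prolonged treatment period has been chosen to follow pre dialytic values of inflammatory mediators".

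Two rules cover the T7 data. Under secondary analyses, 17.4 states: "Secondary outcome variables will be analysed in the same way as the primary endpoint". The primary analysis is a within-patient comparison of the two membranes, and the synopsis also prescribes identical methods for secondary endpoints. But 4.2 says: "Note that Phase 3 is not part of the cross over design". Section 2.3, the synopsis and the exploratory part of 17.4 all call the Phase 3 analysis exploratory.

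**The concern.** A treatment coefficient fitted alongside a time factor is a weighted average of the treatment effects at the three times. It answers the 3-month question only if the effect is the same at all of them. Section 1.3 justifies Phase 3 by expecting the opposite for soluble mediators. The named hypothesis can therefore err in both directions: a 4-week effect that has faded by T7 can still give a significant Phase 3 treatment effect and be read as a 3-month benefit, and an effect that appears only late is averaged with earlier null data.

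The second problem is status and method. Each patient has one T7 sample (7.3, before session 61), taken on one membrane. No within-patient MCO versus HF contrast exists there, yet the rule for secondary outcomes makes no exception for T7. A reader cannot tell whether a 3-month result will be reported as secondary or as exploratory, or from which model.

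**Working it through.** **Inputs from the protocol.** Section 17.1.1 takes a within-patient effect size of 0.5 (mean difference over its SD) from the earlier study, and states: "Assuming a power of 80%, a level of significance of 0.05 (two-sided) we need 34 evaluable patients". It then allows for 30% loss, so that 50 allocated leave 35. Section 10.1: 1:1 allocation. Section 7.3: one T7 sample per patient.

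**Assumed, because the protocol does not give them.** The three time levels, the correlation ρ between a patient's time points (0.3 to 0.7, with independence as a limit) and its structure. I also take it that Phase 3 continues the phase 2 membrane. This agrees with 17.4, which calls Phase 3 a prolongation, and with 4 + 8 = 12 weeks. The weights below ignore the baseline and centre adjustment.

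**Step 1: the plan's own figure.** A paired t-test with effect 0.5 and two-sided 0.05 has power 0.795 at n = 33 and 0.808 at n = 34. Drop-out: 34 / 0.7 = 48.6, so 49 against the stated 50; 50 × 0.7 = 35. The figure reproduces, but for the within-patient contrast only.

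**Step 2: what the pooled coefficient estimates, levels T3/T6/T7.** The sequences are MCO-HF-HF and HF-MCO-MCO, so the treatment difference between sequences is d = (−1, 1, 1). With a free mean at each time and working correlation R, time j has weight d_j(R⁻¹d)_j / (d′R⁻¹d).

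- Exchangeable, with c = ρ/(1 + 2ρ): weights (1 + c, 1 − c, 1 − c)/(3 − c). At ρ = 0.5, c = 0.25, so 1.25/2.75 = 0.455 and 0.75/2.75 = 0.273.
- AR(1): weights (1 + ρ, 1 + ρ², 1 − ρ)/(3 + ρ²). At ρ = 0.5, T7 has 0.5/3.25 = 0.154.

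| ρ | Exchangeable T3 / T6 / T7 | AR(1) T3 / T6 / T7 |
|---|---|---|
| 0 | 0.333 / 0.333 / 0.333 | 0.333 / 0.333 / 0.333 |
| 0.3 | 0.422 / 0.289 / 0.289 | 0.421 / 0.353 / 0.227 |
| 0.5 | 0.455 / 0.273 / 0.273 | 0.462 / 0.385 / 0.154 |
| 0.7 | 0.477 / 0.262 / 0.262 | 0.487 / 0.427 / 0.086 |

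**Step 3: what this does to a result.** Let the 4-week effect be −0.5 at T3 and T6.

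| True T7 effect | Independence | Exchangeable 0.5 | AR(1) 0.5 |
|---|---|---|---|
| 0 | −0.33 | −0.36 | 0.846 × (−0.5) = −0.42 |
| −0.5 | −0.50 | −0.50 | −0.50 |
| −1.0 | −0.67 | −0.64 | −0.42 − 0.154 = −0.58 |

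Only the constant-effect row returns the T7 effect.

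**Step 4: the other reading, T4/T6/T7.** Now d = (1, 1, 1). Independence and exchangeable correlation give one third to each time. AR(1) gives (1, 1 − ρ, 1)/(3 − ρ), so T7 has 1/2.7 = 0.37, 1/2.5 = 0.40 and 1/2.3 = 0.43 at ρ = 0.3, 0.5 and 0.7. T4 always has the same share as T7, although it precedes phase 2 treatment and its effect is zero. With equal weights and −0.5 at T6, a T7 effect of −1.0 gives (0 − 0.5 − 1.0)/3 = −0.50, and a T7 effect of 0 gives −0.17.

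**Step 5: precision of the T7 contrast.** It compares about 17 with 18 patients. Carrying over the 4-week effect, 0.5 SD of a within-patient difference is 0.5 × √(2(1 − ρ)) between-patient SD: 0.592, 0.500 and 0.387 at ρ = 0.3, 0.5 and 0.7. Baseline adjustment multiplies the residual SD by √(1 − ρ²). Power is then about 0.43, 0.38 and 0.34. Reaching 80% would take about 41, 48 and 54 patients per arm (normal approximation).

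**The case against.** The strongest reply is that 17.4 does plan to look at the treatment-by-time interaction. A model with that term can yield an effect at T7, and a pooled effect with an interaction check is a conventional exploratory approach. This stands in part: the plan is not blind to an effect that changes over time. But the interaction is neither the named hypothesis nor tied to T7. With the precision in step 5, a non-significant interaction would be weak evidence that the effect is constant.

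Second, factor levels, working correlation and contrasts are commonly left to the SAP, which is not available here. Agreed, and the missing level names are not the complaint. What matters is that the protocol itself fixes the hypothesis, and that hypothesis misses the endpoint.

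Third, the sizes rest on assumed correlations and omit baseline adjustment. They do, so they are shown as ranges. T4 is also an unlikely outcome level, because the synopsis uses it as the phase 2 baseline. On T3/T6/T7, both weight formulas keep T7 at or below one third for any ρ of zero or more.

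Fourth, 1.3 expects a slower response only for soluble mediators and treats 4 weeks as adequate for TNF-α mRNA. The dilution argument is therefore weaker for the mRNA endpoints.

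A reader might also infer that the T7 secondary endpoints cannot be analysed under the stated rule at all. The document does not support that. A generalized linear model or GEE adjusted for baseline and centre can be fitted at T7 as a between-group comparison, and 17.4 gives Phase 3 its own model. Only the within-patient contrast is unavailable.

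**Conclusion.** The concern holds in a limited form. The named Phase 3 hypothesis is a time-averaged effect and does not estimate the 3-month effect unless the effect is constant. If the levels are T3/T6/T7, T7 contributes about 26 to 33% (independence, or exchangeable up to 0.7) or 9 to 23% (AR(1), ρ 0.7 to 0.3). These shares depend on correlations that the protocol does not give. The double status of T7 needs no assumption, since it follows from 2.3, 3.2, 4.2 and 17.4 read together.

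A reader might infer that the trial's main conclusion is at risk. It is not: the primary endpoint, its sample size and its error control do not involve T7, and this is a pilot whose Phase 3 analysis is exploratory. The point should be fixed because doing so is cheap and prevents a misattributed 3-month claim, but it is not a condition for a sound primary analysis.

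**What to change.** In 17.4:

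1. Name the three time levels.
2. Make the MCO minus HF contrast at T7 the Phase 3 hypothesis and the estimate for every 3-month endpoint. Take it from the treatment-by-time model, or from a T7 model adjusted for baseline and centre.
3. State that it compares patients between the randomised sequences and is not covered by the sample size calculation.
4. Exempt T7 endpoints from the rule that secondary outcomes follow the primary analysis.
5. Call T7 either secondary or exploratory, and use that label in the synopsis, 2.3, 3.2 and 17.4.

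The cost is a few sentences and one contrast statement, with no new data. The price is a wider confidence interval at T7, which reflects what about 35 evaluable patients can show in a between-patient comparison. The pooled effect can stay as a supporting summary.
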